## Abstract

***Background*:**

Approximately one-third of patients with symptomatic severe aortic valve stenosis who are scheduled for transcatheter aortic valve implantation (TAVI) have some degree of cognitive impairment. TAVI may have negative cognitive effects due to periprocedural micro-emboli inducing cerebral infarction. On the contrary, TAVI may also have positive cognitive effects due to increases in cardiac output and cerebral blood flow (CBF). However, studies that systematically assess these effects are scarce. Therefore, the main aim of this study is to assess cerebral and cognitive outcomes in patients with severe aortic valve stenosis undergoing TAVI.

***Study design*:**

In the prospective CAPITA (**CA**rdiac Out**P**ut, Cerebral Blood Flow and Cognition **I**n Patients With Severe Aortic Valve Stenosis Undergoing **T**ranscatheter **A**ortic Valve Implantation) study, cerebral and cognitive outcomes are assessed in patients undergoing TAVI. One day before and 3 months after TAVI, patients will undergo echocardiography (cardiac output, valve function), brain magnetic resonance imaging (CBF, structural lesions) and extensive neuropsychological assessment. To assess longer-term effects of TAVI, patients will again undergo echocardiography and neuropsychological assessment 1 year after the procedure. The co-primary outcome measures are change in CBF (in ml/100 g per min) and change in global cognitive functioning (Z-score) between baseline and 3‑month follow-up. Secondary objectives include change in cardiac output, white matter hyperintensities and other structural brain lesions. (ClinicalTrials.gov identifier NCT05481008)

***Conclusion*:**

The CAPITA study is the first study designed to systematically assess positive and negative cerebral and cognitive outcomes after TAVI. We hypothesise that TAVI improves cardiac output, CBF and cognitive functioning.

**Supplementary Information:**

The online version of this article (10.1007/s12471-023-01826-8) contains supplementary material, which is available to authorized users.

## Introduction

Aortic valve stenosis is the most common valvular heart disease requiring intervention in Europe and the USA [1, 2]. Most cases of aortic valve stenosis are caused by calcification, leading to a rising prevalence of aortic valve stenosis in a continuously aging population [2]. Severe aortic valve stenosis causes left ventricular (LV) pressure overload and ventricular remodelling, which has a poor prognosis. If left untreated, patients will experience heart failure, functional deterioration and ultimately death [1, 2]. In addition to physical symptoms, patients with symptomatic severe aortic valve stenosis have considerably lower cognitive test scores than controls without aortic valve stenosis [3].

Transcatheter aortic valve implantation (TAVI) is a percutaneous treatment for severe aortic valve stenosis, nowadays established for low-risk patients [2]. One-third of patients scheduled for TAVI have some form of cognitive impairment prior to the intervention [3–6]. TAVI has been noted to worsen cognitive functioning but can also improve it [4–10]. Cognitive decline may be caused by cerebral emboli that can dislodge periprocedurally from the calcified aorta and aortic valve, thereby inducing brain infarctions detectable on magnetic resonance imaging (MRI) in up to 76% of patients after TAVI [5, 9]. Conversely, cognitive functioning may improve in a subset of patients after TAVI, particularly in those with baseline cognitive impairment and smaller aortic valve areas [4, 6–8, 10]. Improved cognitive functioning has been observed in multiple studies [6, 8, 10], but the underlying mechanism has not been elucidated. It has been hypothesised that restoration of impaired cardiac output after TAVI improves cerebral blood flow (CBF) and potentially also cognitive functioning [6–9].

The CAPITA (**CA**rdiac Out**P**ut, Cerebral Blood Flow and Cognition **I**n Patients With Severe Aortic Valve Stenosis Undergoing **T**ranscatheter **A**ortic Valve Implantation) study is the first larger-scale study aimed at the systematic assessment of CBF and cognition in patients undergoing TAVI (Fig. 1). We hypothesise that TAVI improves cardiac output, CBF and cognitive functioning.

**Fig. 1 Fig1:**
[figure not shown]
Infographic

## Methods

### Measurements

The prospective CAPITA study evaluates the effect of TAVI treatment on cardiac output, CBF, structural brain lesions and cognitive functioning. Prior to TAVI and at 3‑month follow-up, patients will undergo echocardiography (cardiac output, valve function, LV function), brain MRI (CBF using arterial spin labelling (ASL), white matter hyperintensities (WMH), structural lesions) and extensive neuropsychological testing. To evaluate longer-term haemodynamic and cognitive effects of TAVI, echocardiography and neuropsychological testing will be performed again 1 year after TAVI. Baseline measurements will be taken on the day before scheduled TAVI. Follow-up assessments will be performed during an outpatient clinic visit and are combined with a routine cardiologist consultation. Figure 2 displays the study timeline. The CAPITA study is registered at ClinicalTrials.gov (identifier NCT05481008).

**Fig. 2 Fig2:**
[figure not shown]
Timeline of CAPITA study. *TAVI* transcatheter aortic valve implantation, *MRI* magnetic resonance imaging

### Objectives

The co-primary outcome measures are change in global CBF (in ml/100 g per min) on ASL-MRI and change in global cognitive functioning (Z-score) between baseline and 3‑month follow-up. We will also assess the relation between these co-primary outcome measures and their association with cardiac output [11].

In addition, we will explore determinants of impaired cognitive functioning prior to TAVI, e.g. demographics/risk profile, cardiac functioning and brain injury markers. Moreover, we will explore determinants of change in cognitive functioning after TAVI. As the post-procedural cognitive effects of TAVI may be transient [4, 5, 10], we will assess cognitive functioning again 1 year after TAVI.

We will assess the development and possible regression of WMH on Fluid Attenuated Inversion Recovery (FLAIR) MRI (volume and number at baseline and follow-up). WMH are a manifestation of cerebral small vessel disease, which are associated with increased risk of cognitive impairment and stroke [12]. Moreover, we will assess atrophy (brain volume on structural T_1_-weighted imaging), infarcts (structural T_1_-weighted imaging, FLAIR and diffusion-weighted imaging (DWI)) and bleeds and microbleeds (susceptibility-weighted imaging (SWI)).

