### Patient population

Aortic valve stenosis is defined according to the most recent European Society for Cardiology Guidelines [2]. All consecutive patients scheduled for TAVI at the Amsterdam University Medical Centres (Amsterdam UMC) in Amsterdam, the Netherlands will be screened for study inclusion and approached for study participation at the outpatient clinic. Tab. 1 shows the inclusion and exclusion criteria for the study.

**Table 1 Tab1:** Inclusion and exclusion criteria of the CAPITA study

*Inclusion criteria*	
1	Presence of severe symptomatic aortic valve stenosis and eligible for TAVI
2	Able and willing to give informed consent
3	Aged > 18 years
*Exclusion criteria*	
1	Presence of an MRI contra-indication
2	Known neurological disease, excluding cerebrovascular events without sequelae
3	Active malignant disease
4	Insufficient mastery of the Dutch language
5	Non-atherosclerotic vascular disease (e.g. vasculitis)
6	Dialysis treatment for renal failure
7	Planned surgery with general anaesthesia within 3 months after TAVI

*TAVI* transcatheter aortic valve implantation, *MRI* magnetic resonance imaging

The Amsterdam UMC is a tertiary referral hospital where approximately 350 TAVI procedures per year are performed. A multidisciplinary Heart Team decides whether a patient is eligible to undergo TAVI and selects the access route and valve type. Transfemoral access with local anaesthesia is the default approach. If transfemoral TAVI is not feasible, transaortic access is also performed. Patients will be treated with the balloon-expandable Sapien 3 or Sapien 3 Ultra (Edwards Lifesciences Inc., Irvine, CA, USA) or the self-expandable Navitor (Abbott, Abbott Park, IL, USA) or Evolut R (Medtronic Inc., Minneapolis, MA, USA) transcatheter heart valve devices.

Patients will serve as their own controls: baseline measurements in the presence of severe aortic valve stenosis are compared with post-TAVI follow-up measurement. A control group with comparable aortic valve stenosis seems to be unfeasible, as we believe it is not ethical to delay TAVI in patients with a clinical treatment indication. Time intervals for follow-up assessments are 4 weeks before or after the scheduled visit.

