### Sample size

Based on our pilot data [11], we hypothesise a 10% increase in CBF after TAVI. With an 80% power and α of 0.05, the required sample size is 126. If a TAVI procedure is complicated by the need for permanent pacemaker implantation, subsequent MRI follow-up will be contra-indicated. In addition, some patients will not be able to take part in all follow-up measurements due to concomitant disease, institutionalisation or death. As we estimate 21% of the patients will not be able to undergo follow-up MRI, a total of 152 patients are needed.

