### Statistical analysis

Clinical data will be entered at CastorEDC.com to create the final dataset. Continuous variables will be tested for normality distribution with visual inspection and the Shapiro-Wilk test. Accordingly, differences between baseline and 3‑month follow-up in CBF, as well as cognitive global and domain-specific Z‑scores, will be tested with the paired-samples *t*-test or Wilcoxon signed-rank test.

Change in global CBF (ml/100 g per min increase from baseline) will be assessed as a predictor of change in cognitive functioning (Z-score) using mixed models analysis adjusted for sex, age and education. Additionally, change in cardiac output (in l/min) will be assessed as a predictor of change in CBF with mixed models analysis. Other clinical parameters, including blood pressure, will be assessed as potential confounders of change in CBF and cognitive functioning. Finally, we will examine the association of 1‑year cognitive Z with CBF and cognitive functioning during prior visits.

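### Two co-primary outcomes are tested, but the 126 patients and 80% power support CBF alone at an unadjusted 0.05

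*Protocol article*

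**What the plan says.** Under Objectives, the protocol article gives two outcomes equal standing: "The co-primary outcome measures are change in global CBF (in ml/100 g per min) on ASL-MRI and change in global cognitive functioning", both from baseline to 3 months. The Introduction expects benefit on both: "We hypothesise that TAVI improves cardiac output, CBF and cognitive functioning".

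The Sample size section uses only one of them. It starts from CBF, "Based on our pilot data [11], we hypothesise a 10% increase in CBF after TAVI", and continues "With an 80% power and α of 0.05, the required sample size is 126". The total follows: "As we estimate 21% of the patients will not be able to undergo follow-up MRI, a total of 152 patients are needed". The article gives no effect size, SD or power for global cognition, and no SD for CBF change.

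The design has a single group: "Patients will serve as their own controls: baseline measurements in the presence of severe aortic valve stenosis are compared with post-TAVI follow-up measurement" (Patient population). Under Statistical analysis, the before-after differences in CBF and in the cognitive Z-scores "will be tested with the paired-samples *t*-test or Wilcoxon signed-rank test". That section gives no alpha per test, no order of testing, and no rule on whether one or both outcomes must succeed. The value 0.05 appears once, in the CBF sample size sentence.

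**The concern.** The calculation spends the whole 0.05 on one of two outcomes of equal rank. What the stated 5% and 80% then mean depends on how the two results are combined:

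- **Either suffices, both at 0.05:** there are two chances of a false claim, so the error rate for the pair exceeds 5%.
- **Either suffices, alpha shared:** CBF may be tested below 0.05, so its power falls below the planned value.
- **Both required:** error is controlled, but 80% describes one component and not the chance of success on both.
- **CBF first, then cognition:** 5% error and the planned CBF power both survive.

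If the rule is not settled before the results are seen, one significant outcome could be presented as the study's success at an error rate that nobody declared. The sample size can no longer absorb this, because the Current status section puts the last baseline visit in October 2022. What can still be changed is the rule and the power statement.

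**Working it through.** **Inputs.** From the Sample size section: alpha 0.05, power 80%, 126 evaluable, 21% without follow-up MRI, 152 in total. Assumptions: two-sided test (sidedness is not stated), normal approximation, and 0.05 for the cognitive test where the either-outcome case is examined.

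**1. The plan's own 126.** For a paired comparison, n = ((z₁₋α/₂ + z_power) / d)², where d is the mean change divided by the SD of change. No SD is given, so 126 cannot be rebuilt from the stated inputs, only solved backwards:

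d = (1.960 + 0.842) / √126 = 2.802 / 11.225 = 0.2496

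A 10% mean change then implies an SD of change of 10 / 0.2496 ≈ 40%. The result is sensitive to this: an SD of 35% needs 97 patients, 40% needs 126 and 45% needs 159.

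**2. The plan's own 152.** 126 × 1.21 = 152.5, which matches the stated total. Allowing for 21% loss requires division: 126 / 0.79 = 159.5, so 160. Conversely, 152 × 0.79 = 120.1, so about 120 patients will have both scans.

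**3. Family-wise error if either outcome suffices, each at 0.05, no true effect on either.** If independent: 1 − 0.95² = 0.0975. With correlated test statistics (bivariate normal):

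| Correlation | Family-wise error |
|---|---|
| 0 | 9.75% |
| 0.3 | 9.5% |
| 0.5 | 9.1% |
| 0.7 | 8.3% |
| 0.9 | 7.0% |

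The upper bound is 0.05 + 0.05 = 10%. The article gives no correlation, so the range is the result.

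**4. CBF power.** Power = Φ(d√n − z₁₋α/₂), with d = 0.2496, z = 1.960 for alpha 0.05 and z = 2.241 for alpha 0.025.

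| Evaluable n | d√n | Power at 0.05 | Power at 0.025 |
|---|---|---|---|
| 126 | 2.802 | Φ(0.842) = 80% | Φ(0.560) = 71% |
| 120 | 2.734 | Φ(0.774) = 78% | Φ(0.493) = 69% |

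Under Holm, CBF is tested at 0.05 whenever cognition passes 0.025, and must otherwise pass 0.025 itself. Its power therefore lies between the two columns: 71% to 80% at 126, and 69% to 78% at 120. To guarantee 80% at 0.025, n = ((2.241 + 0.842) / 0.2496)² ≈ 153 evaluable.

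**5. Joint power if both are required.** It cannot exceed the power of either component, so at most 80% at 126 and 78% at 120. Below that bound no single figure can be given, because the cognition inputs are absent. Purely as illustration, with CBF power 80% and independent tests, an assumed cognition power of 50%, 80% or 99% gives joint power of 40%, 64% or 79%. At correlation 0.5 the same assumptions give 46%, 69% and 80%.

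**The case against.** The strongest reply is that much of this rests on silence. Only an article is at hand, and a multiplicity rule is commonly left to the SAP or full protocol. That stands: the absence of a rule from the article is not in itself an error. What the article does state is a sample size and power that use one of two co-primary outcomes at full alpha, and a total that does not deliver the 126 under its own loss rate. No SAP wording changes those figures.

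A reader might infer that no interpretation can honour both the stated alpha and the stated power. The documents do not support this. A CBF-first sequence keeps both. Requiring both outcomes also keeps error at or below 5%, and 80% remains true as the CBF power, which is all the Sample size section claims. The article excludes neither reading.

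A reader might also infer that the study has an error rate of 9.75%. That needs three things the article does not say: that cognition is tested at 0.05, that either outcome alone counts as success, and that the tests are independent. Independence is doubtful, since the Objectives section plans to study how the two outcomes relate. The figure also applies only when neither outcome truly changes.

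Finally, a gain from repeated cognitive testing might seem to strengthen the case. It would be a bias, which no multiplicity adjustment removes, so it plays no part here.

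It is also fair to say that the 21% concerns follow-up MRI. The 120 is therefore the CBF count and says nothing about how many patients will have cognitive data.

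**Conclusion.** The point holds in limited form. The stated 126 patients, 80% power and alpha 0.05 support CBF alone, unadjusted; cognition is co-primary without any power basis. With 152 enrolled and 21% loss, the CBF power to expect is about 78%, not 80%.

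The consequence for error depends on a success rule that the article does not give: about 7% to 10% for correlations from 0.9 down to 0 if either outcome may be claimed unadjusted, and no more than 5% if both are required or CBF is tested first. The power results rest on a two-sided test and on d of about 0.25 solved back from 126. The error results assume both tests at 0.05 and no true effect on either outcome. This is worth correcting before analysis, but it does not invalidate the design.

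**What to change.** Before the 3-month analysis:

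1. Declare the success rule for the two co-primary outcomes: either, both, or CBF first.
2. If either may be claimed on its own, use Holm: the smaller p-value against 0.025 and, if that passes, the other against 0.05. If both must succeed, keep 0.05 for each and say that 80% is not the joint power.
3. Restate the power in the Sample size section as applying to CBF only: about 78% at 120 evaluable patients with 0.05 unadjusted, or between about 69% and 78% under Holm. Give the SD of CBF change behind the 126, and say that cognition was not powered.

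This takes a few sentences and no new patients or data. The price is a slightly stricter threshold for the first outcome under Holm and a slightly lower stated power. If a rule already exists in the SAP or full protocol, citing it settles items 1 and 2; item 3 remains.

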### Patient population

Aortic valve stenosis is defined according to the most recent European Society for Cardiology Guidelines [2]. All consecutive patients scheduled for TAVI at the Amsterdam University Medical Centres (Amsterdam UMC) in Amsterdam, the Netherlands will be screened for study inclusion and approached for study participation at the outpatient clinic. Tab. 1 shows the inclusion and exclusion criteria for the study.

**Table 1 Tab1:** Inclusion and exclusion criteria of the CAPITA study

*Inclusion criteria*	
1	Presence of severe symptomatic aortic valve stenosis and eligible for TAVI
2	Able and willing to give informed consent
3	Aged > 18 years
*Exclusion criteria*	
1	Presence of an MRI contra-indication
2	Known neurological disease, excluding cerebrovascular events without sequelae
3	Active malignant disease
4	Insufficient mastery of the Dutch language
5	Non-atherosclerotic vascular disease (e.g. vasculitis)
6	Dialysis treatment for renal failure
7	Planned surgery with general anaesthesia within 3 months after TAVI

*TAVI* transcatheter aortic valve implantation, *MRI* magnetic resonance imaging

The Amsterdam UMC is a tertiary referral hospital where approximately 350 TAVI procedures per year are performed. A multidisciplinary Heart Team decides whether a patient is eligible to undergo TAVI and selects the access route and valve type. Transfemoral access with local anaesthesia is the default approach. If transfemoral TAVI is not feasible, transaortic access is also performed. Patients will be treated with the balloon-expandable Sapien 3 or Sapien 3 Ultra (Edwards Lifesciences Inc., Irvine, CA, USA) or the self-expandable Navitor (Abbott, Abbott Park, IL, USA) or Evolut R (Medtronic Inc., Minneapolis, MA, USA) transcatheter heart valve devices.

Patients will serve as their own controls: baseline measurements in the presence of severe aortic valve stenosis are compared with post-TAVI follow-up measurement. A control group with comparable aortic valve stenosis seems to be unfeasible, as we believe it is not ethical to delay TAVI in patients with a clinical treatment indication. Time intervals for follow-up assessments are 4 weeks before or after the scheduled visit.

### Cardiac output

Cardiac output will be assessed by echocardiographic Doppler measurements of the LV outflow tract velocity time integral, which has been validated against thermodilution, pulmonary artery catheter measurements and cardiac MRI [13–15]. Transthoracic echocardiography (GE Medical Systems, Horten, Norway) will be performed by trained echocardiographists from the Amsterdam UMC according to the procedural guidelines of the European Association of Cardiovascular Imaging [16]. All echocardiographs will be evaluated by an independent core laboratory blinded for outcomes using an automatic segmentation method and visually checked by the same physician, who is blinded to clinical data and outcomes.

### Brain magnetic resonance imaging

Brain MRI will be performed using the same 3T MRI scanner (Ingenia, Philips, Best, the Netherlands) at baseline and 3‑month follow-up. Tab. 2 shows the sequences included in the MRI protocol (structural T_1_-weighted imaging, FLAIR, ASL, SWI and DWI).

**Table 2 Tab2:** Magnetic resonance imaging study protocol

Scanning sequence	Objective
T_1_-weighted	Brain volume, segmentation purposes
Fluid attenuation inversion recovery T_2_-weighted	White matter hyperintensities
Arterial spin labelling	Cerebral blood flow (labelled image)
M0^a^	Cerebral blood flow (control image)
Q flow	Carotid artery flow (in ml/min)
Susceptibility-weighted imaging	Bleeds and microbleeds
Diffusion-weighted imaging	Recent and semi-recent infarctions

^a^ M0 is control image of cerebral blood flow measurement

ASL-MRI assesses global and regional CBF (in ml/100 g per min) using an endogenous tracer [17]. The blood will be magnetically labelled in the carotid artery, creating a labelled image and control image. Both sequences include measurements of the static brain, and the difference between these sequences is the magnetisation of inflowing blood. The ASL-MRI acquisition is shown in Fig. 3. Time of day during scanning, room temperature and visuo-auditory stimuli will be kept similar during baseline and follow-up visits. Patients will be instructed to refrain from caffeine for 3 h and from alcohol and smoking for 12 h prior to the scan [18]. ASL-MRI analyses will be performed by an independent core laboratory using pipelines, which are blinded to clinical data and whether scans were performed at baseline or follow-up. Analyses are corrected for brain volume and partial volume effects.

**Fig. 3 Fig3:**
[figure not shown]
Arterial spin labelling magnetic resonance imaging acquisition. **a** Unlabelled scan, **b** endogenous tracer labelling in carotid artery, **c** labelled blood enters cerebral circulation and **d** labelled scan. Cerebral blood flow = labelled scan—unlabelled scan

WMH are quantified using the Lesion Segmentation Toolbox, an automated segmentation method that uses structural T_1_-weighted imaging and FLAIR sequences [19]. With these segmentations, we will compute WMH location and volumes (in ml). More details of the MRI protocol can be found in Table S1 in the Electronic Supplementary Material.

